#### Data safety monitoring board

A Data Safety Monitoring Board chaired by the director of the Department of Critical Care Medicine (XX) of Jinhua Municipal Central Hospital, comprising experts in clinical trials, biostatistics and intensive care, has been established. The board will review data on patient characteristics, compliance and study outcome in an interim analysis (based on the availability of primary outcomes for 350 patients). The study will be terminated if one arm turns out to be harmful compared to the other.

Adverse events were considered to be: hematoma, pneumothorax, arterial emboli, catheter-relatedbloodstream infection, hemorrhage, pseudoaneurysm or arrhythmia.

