## Methods

The study is designed as a prospective randomized controlled multi-center trial in the ICUs of four tertiary academic centers. These are mixed ICUs treating both surgical and medical patients. The total number of beds is 96. The study will last for a period of 2 years. The end of the study is defined by the last follow-up of the last enrolled patient. The study was approved by the ethics committees of the participating institutions.

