#### Control intervention

Patients in the control arm will not receive PiCCO monitoring, but a central venous catheter is routinely inserted. If the CVP is less than 8 mmHg, a 500 ml bolus of hydroxyethyl starch 130/0.4 (Voluven®) is infused over 30 min aiming to give a CVP of 8 to 12 mmHg. The bolus can be repeated if the target is not reached. If the CVP exceeds 12 mmHg, furosemide and/or nitroglycerin and/or dobutamine are used at the discretion of the attending physician. If MAP is less than 60 mmHg, norepinephrine is started at 0.05 μg.kg^-1^.min^-1^ with the option to increase at an increment of 0.05 μg.kg^-1^.min^-1^. If MAP > 100 mmHg, nitroglycerin is given at the dose range of 0.5 to 3.0 μg.kg^-1^.min^-1^. An RBC transfusion is triggered when Hb<7 g.dl^-1^. ScvO_2_ is maintained >70% (Figure
2).

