#### Ethical aspects

The study has been approved by the ethics committees of Jinhua Municipal Central Hospital, the Traditional Chinese Medical Hospital of Jinhua City, Dongyang People’s Hospital and the First People’s Hospital of Yongkang City. The research will be explained in detail to the patient or the next-of-kin prior to enrollment. The explanation will include the type and method of the study, the complications of PiCCO monitoring and the potential benefit or harm of the intervention. Written informed consent will be obtained from the patients or their surrogates. The patient or surrogate can withdraw from the study at any time.

The study is conducted according to the Declaration of Helsinki.

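### The Data Safety Monitoring Board is chaired by the head of critical care at one of the four participating hospitals, whose department may go on enrolling and treating patients after the interim look at outcomes

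*Protocol article*

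**What the plan says.** In the protocol article, the section Data safety monitoring board says that the board has been set up and is "chaired by the director of the Department of Critical Care Medicine" at Jinhua Municipal Central Hospital. Its members have expertise in trials, biostatistics and intensive care. On its task: "The board will review data on patient characteristics, compliance and study outcome", at an interim analysis when 350 patients have a primary outcome. The trial is to end if one arm proves harmful relative to the other.

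The hospital's place in the trial follows from two sections. Methods describes a "prospective randomized controlled multi-center trial in the ICUs of four tertiary academic centers" and adds: "The study was approved by the ethics committees of the participating institutions". Ethical aspects names four approving hospitals, with the chair's hospital first: "The study has been approved by the ethics committees of Jinhua Municipal Central Hospital".

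Two decisions in care are left to the physicians in charge. Under Control intervention, when CVP is above 12 mmHg, "furosemide and/or nitroglycerin and/or dobutamine are used at the discretion of the attending physician". Under Experimental intervention, the PiCCO system is removed after 48 hours of clinical stability, as judged by the attending physicians.

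The section Blindness reports efforts to mask researchers and participants (a common monitor and a sham cold injection in controls) and says that those who collect baseline and follow-up data are blinded. It does not mention treating physicians.

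**The concern.** A monitoring board is given interim comparative results so that nobody running the trial has to see them. Here the person leading the board also leads a department at a participating center. Once that person knows how mortality compares between the arms, the knowledge sits in a unit that may still be approaching patients and managing both arms.

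Two things are at stake. First, expectations about the result could affect which patients are put forward and how the discretionary parts of care are used, without any written rule being broken. Second, a decision to stop or continue is harder to defend when the chair's own department has a part in the trial. The article gives the stopping criterion as a judgement of harm with no numerical threshold, so the independence of those who make that judgement carries more weight.

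**Working it through.** **Is the chair's hospital a participating center?**
1. Methods: the trial runs in the ICUs of four centers, and the approving ethics committees are those of the participating institutions.
2. Ethical aspects: the approving committees belong to four named hospitals, and the chair's hospital is one of them.
3. Four centers and four hospitals match. The hospital participates, and the chair directs critical care there.

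**Does the board need outcomes by arm?**
1. The board reviews study outcome when 350 primary outcomes are available.
2. The primary endpoint is 30-day all-cause mortality (Study end point).
3. Stopping depends on one arm being harmful relative to the other.
4. That cannot be judged without comparing mortality between arms. The article does not use the words mortality by arm; this is an inference, but one that the stopping rule requires.

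**Can treating physicians tell the arms apart?** The PiCCO algorithm acts on ITBVI and EVLWI, obtained through a thermistor-tipped arterial catheter. The control algorithm acts on CVP. Whoever follows the algorithm works from different data in each arm. This too is an inference, since Blindness says nothing either way about treating physicians.

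**The plan's sample size.** For 40% versus 30% mortality, two-sided 5%, 80% power and 1:1 allocation (assumed), the unpooled formula gives

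n per arm = (1.960 + 0.842)² × (0.40 × 0.60 + 0.30 × 0.70) / 0.10² = 353.2 (unrounded quantiles), rounded up to 354, so 2 × 354 = 708.

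The stated total is reproduced. The pooled-variance formula gives 712.

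**How much of the trial is left at the look?**
- Outcomes available: 350/708 = 49.4%.
- Outcomes pending, all sites: 708 − 350 = 358, and 358/708 = 50.6%.
- Some of the 358 are already enrolled and waiting for day 30. With even accrual over the planned two years (assumed), 708/24 = 29.5 patients a month, so about 30 are in follow-up and 358 − 29.5 = 328.5 are still to enrol.

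**How many of those are at the chair's site?** The article gives no site shares. With assumed shares applied to the 328.5:

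| Assumed share of chair's site | Patients still to enrol there | Percent of 708 |
|---|---|---|
| 10% | 0.10 × 328.5 = 33 | 4.6% |
| 25% (equal sites) | 0.25 × 328.5 = 82 | 11.6% |
| 50% | 0.50 × 328.5 = 164 | 23.2% |

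**What might the chair see?** If the design assumptions hold, with 175 per arm (assumed), the expected deaths are 175 × 0.40 = 70 and 175 × 0.30 = 52.5. The pooled proportion is 122.5/350 = 0.35, and z = 0.10 / √(0.35 × 0.65 × 2/175) = 0.10/0.0510 = 1.96. A difference of that size would be hard for anyone running a participating unit to put out of mind.

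**The case against.** The strongest reply is that the routes to bias are narrow. Eligible patients are enrolled consecutively with sealed opaque envelopes, both algorithms use mostly numeric triggers, data collectors are blinded, and all-cause death is hard to misascertain. Also, a journal article condenses its source: a charter could specify coded arms, closed sessions or recusal of the chair. All of this limits the likely size of any bias. It does not remove the conflict, because the article states who the chair is, and a charter could only add safeguards around that appointment.

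A reader might also infer more than the text supports:
- *That the trial is open.* The article claims masking of researchers, participants and data collectors. The supportable statement is that treating physicians are not named among the masked and act on different data by arm.
- *That 51% of patients are exposed to the chair's influence.* That figure counts pending outcomes at all four sites; only the chair's own site is directly concerned.
- *That the chair's department judges who is moribund, or could switch patients between arms.* Patient selection does not say who judges that exclusion, and no crossover provision appears.
- *That the board ignores adverse events because its list of reviewed data does not mention them.* A full list is commonly left to a charter, and the same section defines the adverse events. No finding follows.

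**Conclusion.** The point holds as a matter of governance: the named chair is not independent of a participating center, and the board's task implies seeing 30-day mortality compared between arms. At that moment up to 358 of 708 primary outcomes (51%) are pending across the four sites. The part still to be enrolled at the chair's own site is about 82 patients (12% of 708) if sites recruit equally and accrual is even; the article supports no firmer number.

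The conclusion rests on two inferences: that a harm comparison needs outcomes by arm, and that recruitment may continue during and after the look, since no pause is described. It does not show that the result would be biased, and no change in the effect estimate, type I error or power has been demonstrated. What is at risk is the credibility of the decision to stop or continue, and the possibility that interim knowledge affects enrolment or discretionary care at one site. It should be corrected, as the trial is still recruiting according to Trial status.

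**What to change.** In the section Data safety monitoring board, give the chair to a member with no role at any of the four participating hospitals. State that nobody who enrols or treats trial patients may see interim data by arm. This should be settled before the look at 350 patients.

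The cost is one edited paragraph and a short delay while an outside chair is appointed. Sample size, significance level and power stay as they are.

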## Background

Hemodynamic monitoring and the associated fluid therapy are of critical importance in the management of critically ill patients. The optimization of fluid status remains a challenge in critical care settings because fluid overload will lead to organ edema and an ensuing increase in mortality
[1,2], whereas inadequate circulating volume will result in insufficient perfusion pressure and oxygen delivery. Therefore, monitoring the fluid status of critically ill patients is very important. Recent decades have witnessed rapid advances in fluid monitoring techniques. Pulmonary artery catheters have been widely used for more than five decades, but unfortunately their usefulness in improving patient outcomes seems disappointing
[3]. The PiCCO system (Pulse index Contour Continuous Cardiac Output, Pulsion Medical Systems, Germany) incorporates a transpulmonary thermodilution technique (TPTD) and continuous pulse contour analysis. It is a minimally invasive technique, which gives beat-by-beat monitoring of cardiac output, and can provide accurate information on volume status and pulmonary edema. Furthermore, the PiCCO monitor is an ‘all-inclusive’ device, which provides a full picture of a patient’s hemodynamic status, including vascular tone, preload, and cardiac function
[4]. However, clinical studies investigating the usefulness of the PiCCO system have mainly focused on intermediate physiological parameters, such as fluid responsiveness, oxygenation and pulmonary edema,
[5,6], and only a few studies have investigated clinical outcomes of patients managed using a PiCCO monitor
[7,8]. Although these studies have promising results, the link between its use and clinical outcomes (for example mortality, length of stay in an ICU, duration of mechanical ventilation) is largely unknown.

Patients with acute respiratory distress syndrome (ARDS) are characterized by increased pulmonary extravascular lung water (EVLW), and may potentially benefit from EVLW monitoring. Simmons *et al*.
[9] noticed that a more negative fluid balance in ARDS patients was associated with improved survival. More recently, numerous studies have demonstrated that elevated EVLW is associated with an increased mortality rate
[10,11]. A recent meta-analysis by our group also supports this notion

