#### Sample size and statistical analysis

We assumed that the overall mortality at 30 days is 40%
[28,29]. A sample size was calculated to detect a 10% difference in mortality at day 30 between the two groups with a two-tailed test, a significance level of 5% and a power of 80%. We plan to include a total of 708 subjects.

Baseline characteristics will be reported. The difference in 30-day mortality between the two groups will be tested using a chi-square test and intention-to-treat (ITT) analysis. Time-to-event variables including length of stay in the ICU, duration of mechanical ventilation and 30-day survival are compared between the two groups using a log-rank test. Multivariate analysis (the Cox proportional hazards regression model) is used to estimate the hazard ratio adjusted for age, severity of illness and disease category. Age and the APACHE II score will be managed as continuous variables. Adverse events will be reported according to the ITT protocol. All tests are two sided and *P*<0.05 is considered to be statistically significant. Statistical analysis will be performed using Stata 11.0 (College Station, TX 77845, USA).

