## Discussion

Fluid therapy is an art in the treatment of critically ill patients. To facilitate treatment and improve patient outcomes, every effort has been made to enhance the technology used for measuring relevant physiological parameters. These parameters allow us to better understand the underlying mechanisms of certain disorders. For instance, in septic shock, hemodynamic monitoring will typically present a low systemic vascular resistance and high or normal-high cardiac output. Intuitively, an understanding of pathophysiological mechanisms will eventually translate into improvements in clinical outcomes. Pulmonary artery catheters (PACs) have been widely used for several decades only because they allow clinicians to get more information regarding hemodynamic status, but without clinical evidence of improved outcomes. In response to this lack of evidence, several randomized controlled trials have been conducted to test the usefulness of PACs in improving clinical outcomes
[31-33]. Unfortunately, all these trials consistently show that PACs do no better than controls regarding patient outcomes, but they increase medical costs significantly. These disappointing results have tempered the enthusiasm for PACs, and a survey showed that the use of PACs decreased by 65% during recent decades
[34-36].

However, the failure of PACs in improving clinical outcomes does not mean that the measurement of hemodynamic parameters is useless. On the contrary, it reflects the limited understanding of the complex hemodynamic characteristics in critically ill patients. With the declining use of PACs, there is an increasing number of alternatives for hemodynamic monitoring. The PiCCO system is one such alternative, which integrates a wide series of both static and dynamic hemodynamic parameters through a combination of TPTD and pulse contour analysis. The PiCCO system has several advantages over a PAC. First, PiCCO is less invasive than a PAC, so that the severe complications attributable to PACs, such as a pulmonary embolism, pulmonary artery rupture and arrhythmia, are less likely to occur
[37]. Furthermore, the arterial canalization required for PiCCO is safe and no significant adverse events for the usually used femoral site have been demonstrated

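### The adverse-event list is closed and mostly covers catheter complications; no item is specific to the fluid, diuretic or vasodilator rules that differ between the arms, and the board's stated review names no adverse events

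*Protocol article*

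**What the plan says.** The section Data safety monitoring board gives the definition: "Adverse events were considered to be: hematoma, pneumothorax, arterial emboli, catheter-relatedbloodstream infection, hemorrhage, pseudoaneurysm or arrhythmia". The sentence has no wording that leaves the list open. The section Sample size and statistical analysis adds: "Adverse events will be reported according to the ITT protocol".

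On monitoring, the same board section says: "The board will review data on patient characteristics, compliance and study outcome in an interim analysis", timed by "based on the availability of primary outcomes for 350 patients". The stopping rule is: "The study will be terminated if one arm turns out to be harmful compared to the other". No measure of harm is attached to it.

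The Background states that the trial assesses a management algorithm driven by PiCCO data. It also names the danger of too much fluid ("fluid overload will lead to organ edema and an ensuing increase in mortality") and the danger of too little, which is poor perfusion pressure and oxygen delivery.

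**The concern.** The safety definition does not match what is randomized. Patients in both arms have a central venous catheter. The arms differ by the thermistor-tipped arterial catheter and by the rules that decide when fluid, diuretic, vasodilator and inotrope are given. The list covers the catheter well and the rules hardly at all.

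If the definition is followed as written, a patient who newly needs renal replacement, or whose kidneys fail without death, has no reportable adverse event. The board is told to act on harm, but neither its list of inputs nor the stopping sentence says which safety data it will see. The primary mortality analysis is unaffected. What is at stake is whether the trial can describe the non-fatal harms of the strategy it tests.

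**Working it through.** **1. Classify the seven listed items.**
- Access or catheter complications (five): hematoma, pneumothorax, arterial emboli, catheter-related bloodstream infection, pseudoaneurysm.
- Could come from the catheter or from treatment (two): hemorrhage and arrhythmia. Arrhythmia is a possible inotrope harm.
- Specific to fluid, diuretic or vasodilator treatment: none.

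**2. Set the arms side by side** (sections Experimental intervention and Control intervention).

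| Treatment | PiCCO arm | Control arm |
|---|---|---|
| Starch bolus | ITBVI below 850 ml/m² | CVP below 8 mmHg |
| Furosemide | EVLWI 10 ml/kg or more | CVP above 12 mmHg, discretionary |
| Nitroglycerin and/or dobutamine | ITBVI above 1000 ml/m², guided by MAP and CI; dobutamine also at CI below 2.5 L/min/m² | CVP above 12 mmHg, discretionary |
| Norepinephrine, nitroglycerin for high MAP, transfusion | same thresholds | same thresholds |

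The control wording is: "furosemide and/or nitroglycerin and/or dobutamine are used at the discretion of the attending physician". The first three rows are the randomized treatment contrast, and no adverse event is specific to the starch, furosemide or nitroglycerin in them.

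**3. Check whether the outcomes fill the gap** (sections Study end point and Secondary outcome measures).
- All-cause 30-day mortality captures fatal harm from any source.
- Vasoactive days, ventilator days and ICU days capture part of the circulatory and respiratory harm.
- Maximum SOFA over 7 days captures part of the organ harm, but as one peak total across organs. If the circulatory score falls while the renal score rises by the same amount, the total does not move. A patient who enters in shock may already have reached the peak. The window is 7 days, while the PiCCO system may stay in place for up to 10.
- No outcome identifies new renal replacement or fluid overload. The Experimental intervention section itself expects renal replacement in these patients, since it sets calibration timing around it.

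**4. Check the board's inputs.** Three kinds of data are named: patient characteristics, compliance and study outcome. Adverse events of any kind, catheter complications included, are not among them.

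**5. Could the planned size show such a harm if it were counted?** First, the plan's own figure. With 40% versus 30%, two-sided 5%, 80% power and unpooled variance:

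n per arm = (1.960 + 0.842)² × (0.40×0.60 + 0.30×0.70) / 0.10² = 7.849 × 0.45 / 0.01 = 353.2, rounded up to 354, or 708 in total.

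This matches the stated 708 (the pooled formula gives 712). I assume 1:1 allocation, hence 354 per arm at the end and 350/2 = 175 at the interim. The documents give no harm rates, so the base rates below are assumptions. The table gives the increase detectable with 80% power, two-sided 5%:

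| Assumed base rate | 354 per arm | 175 per arm |
|---|---|---|
| 5% | 5.7 points | 8.7 points |
| 10% | 7.3 points | 10.8 points |
| 20% | 9.1 points | 13.2 points |
| 30% | 10.1 points | 14.5 points |

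Likewise at 354 per arm (pooled test), 15% versus 25% has 91.6% power and 10% versus 17% has 77.9%. These figures say only that a harm of that order could be compared if it were collected. They do not measure a defect.

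**The case against.** The strongest reply is that in a trial of a treatment algorithm, harm from the algorithm shows mainly in the outcomes. Mortality, SOFA, vasoactive days and ventilator days can all move the wrong way, and all tests are two-sided. The arterial catheter is specific to the PiCCO arm, while both arms use the same drugs, so listing access events is a reasonable choice. An article may also condense a fuller safety section.

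Much of this stands, and it rules out several stronger readings that a reader might infer:
- *Harms of the algorithms would not be compared or counted at all.* Not supported. Fatal harm and part of the organ harm are compared, and hemorrhage and arrhythmia are listed without restriction to the access site.
- *The board must judge harm without relevant data.* Not supported. It sees study outcome, which can reflect algorithm harm. The gap is that no adverse events are named for its review.
- *The list was drawn where the authors expect least harm.* The Discussion does say "the arterial canalization required for PiCCO is safe and no significant adverse events for the usually used femoral site have been demonstrated", but in a comparison with the pulmonary artery catheter. It is no evidence of why the list was chosen.
- *The trial will declare PiCCO-guided care safe on catheter events alone.* The plan announces no such conclusion.

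The appeal to a fuller document carries less weight. The article does not leave the definition out; it states one, and the statement has no opening for other events.

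**Conclusion.** The point holds in a limited form. The stated adverse-event definition does not fit an intervention described as a management algorithm. Non-fatal harms specific to the fluid, diuretic and vasodilator rules, such as new renal failure or renal replacement, are not adverse events under it, and no listed outcome identifies them separately. The board's stated review names no adverse events, although the board is to stop the trial for harm.

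This rests on reading the list as closed, as it is worded, and on the comparison of the two arms' rules. It does not rest on the power figures, which use assumed rates and 1:1 allocation. The primary analysis is not affected, and nothing here judges any dose or treatment threshold.

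**What to change.** 1. Extend the list in the section Data safety monitoring board with a few objectively defined harms of the algorithm treatments. Examples are new start of renal replacement therapy, worsening of the renal SOFA component from baseline, and cumulative fluid balance as a measure of overload.
2. Ascertain them identically in both arms, and not by PiCCO-derived values: lung water is measured only in the PiCCO arm and would give unequal detection. Hypotension is a poor choice, because it defines septic shock at entry.
3. State that the board receives, by arm at the 350-patient interim, these events, the renal and cardiovascular SOFA components, and the existing adverse events. Repeat the table in the final report.

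**Cost.** A few more case report form items, one more safety table, and some chart retrieval for patients already enrolled, since the trial is recruiting. The SOFA components are needed for the total score anyway. The added events partly overlap with the underlying disease (positive fluid balance is itself among the sepsis variables), so they should be read only as between-arm comparisons. Fluid balance needs particular care, because the PiCCO algorithm aims to shift it.
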